# Virtual Interactive Surgical Skills Classroom: Protocol for a Parallel-Group, Noninferiority, Adjudicator-Blinded, Randomized Controlled Trial (VIRTUAL)

**DOI:** 10.2196/28671

**Published:** 2021-07-22

**Keywords:** digital education, digital health, education, surgery, surgical skills, surgical training, surgical, suturing, telemedicine, virtual classroom, virtual training

## Abstract

**Background:**

Traditional face-to-face training (FFT) for basic surgical skills is inaccessible and resource-intensive. Noninteractive computer-based learning is more economical but less educationally beneficial. Virtual classroom training (VCT) is a novel method that permits distanced interactive expert instruction. VCT may optimize resources and increase accessibility.

**Objective:**

We aim to investigate whether VCT is superior to computer-based learning and noninferior to FFT in improving proficiency in basic surgical skills.

**Methods:**

This is a protocol for a parallel-group, noninferiority, randomized controlled trial. A sample of 72 undergraduates will be recruited from 5 medical schools in London. Participants will be stratified by subjective and objective suturing experience level and allocated to 3 intervention groups at a 1:1:1 ratio. VCT will be delivered using the BARCO weConnect software, and FFT will be provided by expert instructors. Optimal student-to-teacher ratios of 12:1 for VCT and 4:1 for FFT will be maintained. The assessed task will be interrupted suturing with hand-tied knots.

**Results:**

The primary outcome will be the postintervention Objective Structured Assessment of Technical Skills score, adjudicated by 2 experts blinded to the study and adjusted for baseline proficiency. The noninferiority margin (*δ*) will be defined using historical data.

**Conclusions:**

This study will serve as a comprehensive appraisal of the suitability of virtual basic surgical skills classroom training as an alternative to FFT. Our findings will assist the development and implementation of further resource-efficient, accessible, virtual basic surgical skills training programs during the COVID-19 pandemic and in the future.

**Trial Registration:**

International Standard Randomized Controlled Trial Number ISRCTN12448098; https://www.isrctn.com/ISRCTN12448098

**International Registered Report Identifier (IRRID):**

PRR1-10.2196/28671

## Introduction

### Background and Rationale

Basic surgical skills are essential to a wide range of medical professionals and aspiring surgeons. Recent advances in technology have facilitated the development of novel virtual training methods. Virtual classroom training (VCT) permits socially distanced interactive expert instruction via live video communication supplemented by concurrent feedback, graphical aids, and polling [1]. We aim to validate VCT as a modality of high-quality surgical skills education by evaluating its efficacy relative to that of the current alternatives.

### Choice of Comparators

The General Medical Council stipulates safe basic wound closure under supervision as a procedural skill–learning outcome for undergraduate medical students [2]. Despite this, wound closure has not been sufficiently incorporated in university curricula, resulting in a deficiency in graduate competence in recent years [3,4]. Student-led surgical societies can deliver extracurricular tutorials on surgical skills; however, accredited, high-quality training can only be attained by professionally run face-to-face training (FFT) courses [5]. FFT is logistically complex, inaccessible, and resource-intensive. Furthermore, the requirement for social distancing during the COVID-19 pandemic has led to the suspension of nonessential FFT programs [6]. Noninteractive computer-based learning (CBL) is a cost-effective alternative. It can be completed independently by students, with the sole requisite of access to equipment and prerecorded training material. CBL is cheaper and more accessible than FFT; however, it does not offer live demonstration, interaction, or feedback. Therefore, it may be less educationally beneficial [7]. VCT may optimize resources and increase training accessibility while retaining the quality of FFT. VCT has the potential to improve the global availability and accessibility of basic surgical skills training; however, its efficacy has not yet been firmly established [8,9].

### Objectives

This trial is designed to assess the effect size of the 3 interventions and test both the superiority of VCT to CBL and its noninferiority to FFT. We hypothesize that the efficacy of VCT will be greater than that of CBL and similar to that of FFT. We also aim to assess and compare the feasibility and accessibility of the 3 training modalities.

### Trial Design

This is a parallel group, adjudicator-blinded, randomized controlled trial. Participants will be divided into 3 groups with an allocation ratio of 1:1:1. Group 1 will undertake noninteractive CBL, group 2 will receive VCT, and group 3 will receive FFT.

## Methods

### Participants, Interventions, and Outcomes

#### Study Setting

Participants will be recruited from across all year-groups within 5 medical schools in London, United Kingdom, to reduce travel requirements during the COVID-19 pandemic. The participating universities include the following: University College London (UCL), Imperial College London, King’s College London, St George’s University of London, and Barts and the London School of Medicine and Dentistry. The opportunity for students to participate will be advertised on the internet by the official student-led surgical societies that represent the 5 medical schools. Eligible individuals will be invited to volunteer through an electronic application form, which will contain a participant information leaflet (PIL), which includes employed methods of data handling and anonymization. The form will request the provision of informed consent and personal data that comprise name, age, sex, university, year of study, and email address for correspondence. The PIL and consent form are attached in Multimedia Appendix 1.

#### Eligibility Criteria

The criteria for inclusion will be current medical student status, availability on specified trial dates, and the ability to access both a PC with an integrated camera and a smartphone with an integrated camera. Outcome adjudicators will have membership of the Royal College of Surgeons degrees and Basic Surgical Skills certification [10].

#### Interventions

Expenses associated with the coordination of the interventions are listed in Table 1. All participants will be provided with a suture pad that contains a 5-cm incision, needle holder, surgical scissors, toothed and nontoothed forceps, a 70-cm-long nylon cord, and 5 silk suture packs. Interventions will have a 2-hour duration. All participants will view a 6-minute noninteractive instructional video that demonstrates the correct interrupted suturing and hand-tying technique with annotations before beginning the intervention.

Individuals in the CBL group will participate in the study from a location of their choice. They will practice independently under self-direction with continued access to the instructional video. They will be continuously monitored by a trial coordinator via the videoconferencing platform Zoom [11]. The VCT group will remotely attend a virtual classroom led by 2 expert instructors using the BARCO weConnect platform [1]. The VCT control room will be located at UCL, and students will log in from a location of their choice from a PC. Participants will be trained with an instructor-to-student ratio of 1:12. A proficiency-based progression model will be followed. Instructors will have a live view of all participants and will utilize graphical instructional aids, annotations, and interactive polling to deconstruct the task and define its key maneuvers. Students will display their own hands while practicing, allowing the instructors to provide them with concurrent feedback and guidance. The FFT group will physically attend a socially distanced classroom at UCL, in line with national government and institutional COVID-19 guidelines. The group will be divided into 6 subgroups (n=4 students each), and each subgroup will be trained by a single instructor and will have an instructor-to-student ratio of 1:4. This ratio has been shown to optimize the educational benefit of FFT [12]. A proficiency-based progression model will again be followed, and instructors will perform a live demonstration of the correct technique and verbally deconstruct the procedure and define its key maneuvers. Students will also receive concurrent feedback and guidance from the instructor while they practice. The same instructors will deliver all 3 interventions; they will provide the video for CBL and implement the training for both the VCT and FFT arms.

**Table 1 table1:** Financial costs associated with the coordination of the intervention.

Item or service	Cost (GB £)
Subscription to the Barco WeConnect platform	186.24
In-person training venue fees	510.00
Suturing equipment	988.41
Personal protective equipment	113.09
Zoom videoconferencing plan	11.99
Total cost	1809.73

#### Outcomes

Baseline characteristics will be collected to facilitate the identification of systematic differences between intervention groups that may increase the risk of bias. Age, year group, sex, and hand dominance will be elicited through a preintervention questionnaire. The primary outcome will be postintervention suturing and hand-tying proficiency, adjusted for preintervention proficiency. After the initial instructional video and again immediately after the intervention, participants will complete an assessment task. The task will include placing 3 interrupted sutures with hand-tied knots by using a single silk suture, with a time limit of 4 minutes. Proficiency will be measured using a validated Objective Assessment of Surgical and Technical Skills (OSAT) used by the Royal College of Surgeons [10]. Scores will be adjudicated by 2 experts blinded to the study design. Proficiency will be defined as the mean value of both adjudicator scores.

Secondary outcomes will be the students’ subjective suturing and knot-tying confidence, perceptions of the intervention, and expenses associated with session attendance. Subjective confidence and perceptions will be elicited through a postintervention questionnaire and measured on a 5-point Likert scale. Expenses will be self-reported by participants.

#### Participant Timeline

Recruitment will begin in November 2020. Randomization and allocation will commence in January 2021. Interventions, data collection, and data analysis will be completed by May 2021, depending on governmental and institutional COVID-19 guidelines.

#### Sample Size

The effect of VCT on OSAT-measured proficiency is not reported in the existing literature. The VCT technology implemented by this trial has been optimized for 24 attendees. A total sample size of 72 individuals (n=24 per intervention group) was therefore selected. A sensitivity power analysis was performed using a 2-tailed dependent samples *t* test. With an *α* and *β* error probability of .05, a minimum detectable effect of 0.769 was computed.

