#### Statistical Methods

Within-group proficiency improvements after the interventions will be analyzed using the dependent *t* test. Between-group postintervention proficiency will be assessed through analysis of covariance with baseline proficiency as a covariate in the regression model. Post hoc analysis will be performed using the Fisher test of least significant difference. The combined hypothesis that VCT is both superior to CBL and noninferior to FFT will be tested at a 95% significance level. The noninferiority margin (*δ*) was defined on the basis of historical data. An observational study investigated the effect of FFT on OSAT scores, with a reported difference of 3.7 (95% CI 2.7-4.7) in mean values [15]. A *δ* of 0.675 was selected to ensure a preserved fraction of 3/4.

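### The only planning figure, a minimum detectable effect of 0.769, applies to pre-post change within one arm and does not describe power for either between-arm hypothesis

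*Protocol article*

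**What the plan says.** The sample size comes from platform capacity: "The VCT technology implemented by this trial has been optimized for 24 attendees", and "A total sample size of 72 individuals (n=24 per intervention group) was therefore selected". The Sample Size section then adds one statistical figure. "A sensitivity power analysis was performed using a 2-tailed dependent samples" *t* test, and with α and β both .05, "a minimum detectable effect of 0.769 was computed". It uses no SD, baseline correlation or noninferiority margin.

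The Objectives section sets two hypotheses, that VCT is superior to CBL and that it is noninferior to FFT. Statistical Methods tests them as a combined hypothesis. The analysis named for comparing arms is ANCOVA: "Between-group postintervention proficiency will be assessed through analysis of covariance with baseline proficiency as a covariate in the regression model". The dependent *t* test appears there only for improvement within each group. The noninferiority margin is in raw OSAT points: δ "of 0.675 was selected to ensure a preserved fraction of 3/4".

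**The concern.** The power statement and the hypotheses concern different quantities. A dependent *t* test asks whether one arm improved from before to after training. All three arms could improve clearly while both trial questions stayed open. The title calls this a noninferiority trial, yet the noninferiority comparison has no planning figure.

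The units also differ. The 0.769 is standardised by the SD of change and is not labelled as such, while the margin is in raw points, so a reader cannot relate one to the other. If precision against the margin turns out poor, a confidence interval that crosses −0.675 is a likely result even when VCT and FFT are equally effective. Without a stated expectation of precision, that result could be misread as evidence that VCT is worse.

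**Working it through.** **Inputs from the article.** 24 per arm, 72 in total (Sample Size); α = .05 two-sided and β = .05 (Sample Size); margin 0.675 points, which is 2.7/4, the lower limit of the historical CI divided by four (Statistical Methods); ANCOVA with baseline as covariate (Statistical Methods).

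**Assumed, because the article does not give them.** Baseline-post correlation ρ of 0.3, 0.5 or 0.7; residual SD of 1, 2 or 3 OSAT points; a true VCT-FFT difference of 0.

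All powers use the noncentral *t* distribution.

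**1. Reproducing 0.769.** Paired *t* test with n = 24, df = 23 and noncentrality dz × √24, where dz is the mean change divided by the SD of change. Solving for power .95 at two-sided .05 gives dz = 0.7688, which rounds to 0.769. The alternatives do not match:

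| Test | Effect at 95% power |
|---|---|
| Paired, n = 24, two-sided | 0.769 |
| Paired, n = 24, one-sided | 0.692 |
| Paired, n = 48, two-sided | 0.531 |
| Paired, n = 72, two-sided | 0.431 |
| Independent, 24 v 24, two-sided | 1.063 |
| Independent, 24 v 24, one-sided | 0.964 |

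So the stated figure is one arm's pre-post change.

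**2. VCT v CBL (superiority), two-sided .05.** For two independent arms, noncentrality is d × √(24/2) = d × √12. Unadjusted, df = 46. For the three-arm ANCOVA, df = 72 − 3 − 1 = 68 and the residual SD is the outcome SD × √(1 − ρ²), so noncentrality is d × √12 / √(1 − ρ²).

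| Analysis | √(1 − ρ²) | d at 95% power | Power at d = 0.769 |
|---|---|---|---|
| Unadjusted | 1 | 1.06 | 74% |
| ANCOVA, ρ = 0.3 | 0.954 | 1.01 | 79% |
| ANCOVA, ρ = 0.5 | 0.866 | 0.91 | 86% |
| ANCOVA, ρ = 0.7 | 0.714 | 0.75 | 96% |

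**3. VCT v FFT (noninferiority at 0.675 points).** SE = SD × √(2/24), noncentrality = 0.675/SE, df = 68. The 95% CI half-width is 1.995 × SE.

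| Residual SD | SE | 0.675/SE | Power, one-sided 2.5% | Power, one-sided 5% | 95% CI half-width |
|---|---|---|---|---|---|
| 1 | 0.289 | 2.34 | about 63% | 75% | 0.58 |
| 2 | 0.577 | 1.17 | 21% | 31% | 1.15 |
| 3 | 0.866 | 0.78 | 12% | 19% | 1.73 |

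Solved for the SD at one-sided 2.5%, 80% power needs a residual SD of at most about 0.82 points, and 95% power at most about 0.64.

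**4. Joint hypothesis.** Both parts must succeed, so joint power cannot exceed the lower of the two.

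**The case against.** The strongest defence is that the article claims nothing about power between arms. It names the dependent test directly before the figure, never prints a 95% power claim for the trial, and does not tie 0.769 to superiority or noninferiority. The within-group *t* test is a planned analysis, and the Objectives include assessing the effect size of each intervention. The number is right for that purpose. All of this stands. The defect is a mismatch between figure and hypotheses, not a miscalculation, and it does not require 0.769 to be removed.

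A reader might infer that superiority power is lower than the article states. The article states none, so that inference fails. The 74% and 1.06 SD also come from an unadjusted test that is not planned. Under the planned ANCOVA, 95% power at 0.769 SD is reached if ρ is about 0.7, a value the article neither states nor excludes.

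A reader might also infer that noninferiority is practically unattainable. That needs an SD the article does not give. One could try to extract it from the historical difference of 3.7 (95% CI 2.7-4.7), but that requires the historical study's sample size and design, which are not stated. A change-score SD would also not be an ANCOVA residual SD.

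Finally, a journal article may leave detail to a fuller document. That covers what is left out. It does not cover the one figure offered as sample-size justification, which belongs to a test that addresses neither hypothesis.

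**Conclusion.** The point holds as a mismatch. The sole planning figure is correct for within-group change in one arm of 24 and uninformative for both trial hypotheses. Only two results are free of outside assumptions: the reproduction of 0.769 as a paired dz, and the unadjusted 1.06 SD for 24 v 24. The ANCOVA range of 1.01 to 0.75 SD depends on the assumed correlation. The noninferiority range of about 63% down to 12% depends on the assumed residual SD, a true difference of zero and a one-sided 2.5% level. At SD 2 or 3 the expected CI half-width exceeds the margin and power is low. At about 0.82 or below, power is 80% or more. The article does not say which case applies, and that is what a planning statement for this trial should address.

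**What to change.** Rewrite the end of the Sample Size paragraph and leave n at 24 per arm:

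- Keep 0.769 but label it as the within-group standardised change (dz) for one arm, and say that it does not bear on the two hypotheses.
- For VCT v CBL, report the between-arm effect detectable at n = 24 per arm under the planned ANCOVA.
- For VCT v FFT, report power and the expected CI half-width against the 0.675-point margin, also under ANCOVA.
- State and justify the SD and baseline-post correlation used, or show a range. The values assumed above are illustrations and should not be adopted as they stand.

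The cost is text only: no extra participants and no change to the analysis or margin. According to the Results section data collection has already started, so this is a matter of reporting, not redesign. The downside is that the stated figures will probably look less favourable.

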#### Recruitment

The application window will be open for 31 days after advertisement. Applicants will be informed of the outcome within 1 week after its closure. From the pool of applicants, a sample of 72 will be selected to participate in the trial. To ensure substantial representation from all 5 centers, 8 participants will be selected at random from each of the medical schools. Further, 32 participants will then be selected randomly from the remaining applicant pool.

### Assignment of Interventions

#### Allocation

A web-based questionnaire will be distributed to the participants to elicit their subjective confidence in their own suturing ability and the quantity of formal (expert-led) and informal (peer-led or independent) suturing training they have previously received. Participants will then be stratified by subjective suturing confidence—measured on a 5-point Likert scale—and objective previous suturing training experience—measured to the nearest hour. Permuted block randomization (block size=3) will be carried out to allocate the participants within each stratum to 1 of the 3 intervention groups. Permutations will be selected by a random number generator. Comprehensive instructions and guidelines to be followed before and during the training sessions will also be provided. Participants who do not want or are unable to participate will be replaced through random selection from the remaining list of applicants where possible.

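### Whole-hour strata with blocks of 3 will usually not deliver the 24 per arm on which delivery is built, and they waste part of the benefit of stratifying

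*Protocol article*

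**What the plan says.** In the protocol article, the Allocation section has participants report their confidence on a five-point scale and "the quantity of formal (expert-led) and informal (peer-led or independent) suturing training they have previously received". Then: "Participants will then be stratified by subjective suturing confidence", together with previous training, which is "measured to the nearest hour. Permuted block randomization (block size=3) will be carried out to allocate the participants within each stratum" to one of the three groups. It gives no hour bands, no upper limit, and no rule for a stratum whose size is not a multiple of 3. People who drop out are replaced at random from the remaining applicants if any are available. How a replacement is allocated is not stated.

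Three other sections rest on equal arms. Trial Design: "Participants will be divided into 3 groups with an allocation ratio of 1:1:1". Sample Size: "A total sample size of 72 individuals (n=24 per intervention group) was therefore selected", because "The VCT technology implemented by this trial has been optimized for 24 attendees". Interventions, for FFT: "The group will be divided into 6 subgroups (n=4 students each"), one instructor to each; VCT has two instructors at 1:12. The Abstract states that both teaching ratios will be kept.

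Study Setting suggests that earlier experience may vary widely: "Participants will be recruited from across all year-groups within 5 medical schools in London".

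**The concern.** Blocks of 3 equalise the arms only when they are full. A stratum with one or two people left over sends them to randomly chosen arms, and these remainders add up across strata. Five confidence levels crossed with every whole hour of training can produce dozens of strata for 72 people, many holding one or two.

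Two things are at stake. First, arm sizes: if VCT or FFT draws 26 or 27, the stated teaching ratio is missed or someone must be moved, and the article does not say which. Second, the purpose of stratifying: a stratum of one person balances nothing, so part of the balance on prior experience is lost.

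**Working it through.** **The plan's own figures.** 3 x 24 = 72; 5 x 8 + 32 = 72 (Recruitment); FFT 6 x 4 = 24; VCT 2 x 12 = 24. All agree on 24 per arm. The detectable effect of 0.769 also reproduces at n = 24 (paired t test, two-sided 0.05, power 0.95: 0.7688), but it does not bear on allocation.

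**Number of strata.** Cells = 5 x number of distinct hour values. Hours 0-10 give 5 x 11 = 55; hours 0-20 give 5 x 21 = 105. Seventy-two people form only 24 full blocks.

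**What leftovers do.** This part needs no assumption about hours. Let k1 strata have one person left over and k2 have two. With k1 = 3 and k2 = 0, equal arms need the three people to land in three different arms: 3!/3^3 = 6/27 = 0.222. With k1 = k2 = 1 the chance is 1/3. By simulation it is 0.066 for k1 = k2 = 6 and 0.035 for k1 = k2 = 12.

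**Simulated allocations.** 72 people, strata = confidence level x whole hour, independent permuted blocks of 3 in each, 2000 runs per row. All spreads are assumptions.

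| Assumed spread | Occupied strata | Incomplete blocks | P(24/24/24) | Mean gap, largest minus smallest arm | P(VCT > 24) |
|---|---|---|---|---|---|
| Confidence even, hours even 0-20 | 52 | 94% | 0.018 | 7.0 | 0.42 |
| Confidence over all five levels, hours geometric, mean 6 | 43 | 84% | 0.015 | 6.2 | 0.45 |
| Confidence even, hours even 0-10 | 40 | 81% | 0.024 | 5.8 | 0.44 |
| Confidence skewed low, hours geometric, mean 3 | 31 | 68% | 0.035 | 5.0 | 0.41 |
| Confidence even, hours even 0-4 | 24 | 52% | 0.052 | 4.0 | 0.39 |
| Mostly lowest confidence, hours geometric, mean 1 | 16 | 42% | 0.060 | 3.6 | 0.39 |
| Mostly lowest confidence, hours rising with confidence | 16 | 42% | 0.077 | 3.4 | 0.35 |
| 85% lowest confidence; 85% at 0 h, rest 1-2 h | 7 | 21% | 0.145 | 2.3 | 0.31 |
| Two confidence levels (90/10); 90% at 0 h, rest 1 h | 3-4 | 10% | 0.306 | 1.5 | 0.25 |

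A second set of assumed spreads, extending to 90% novices, gave 19-76% incomplete blocks, P(24/24/24) of about 3-6% (15% at 90% novices), and VCT or FFT above 24 in 60-75% of runs. In the last row of the table that last figure must be lower: VCT and FFT are symmetric, so it is at most 2 x 0.25 = 0.50.

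**Balance.** The measure is the SD, over allocations, of the standardised VCT-FFT difference in hours. As planned it is 0.15-0.26 in the first seven rows, against about 0.29 for an unstratified 24/24/24 split. Evenly filled 2x2 or 3x2 strata give 0.06-0.07, but that is balance on the band itself, so it flatters them on raw hours.

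**Precision.** SE ratio against 24 v 24 = sqrt[(1/n1 + 1/n2)/(2/24)].
- 20 v 28: sqrt(0.08571/0.08333) = 1.014
- 18 v 28: sqrt(0.09127/0.08333) = 1.047

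**Sorted triplets.** Twenty-four triplets, one member of each to each arm, give 24/24/24 by construction. Sorting on confidence and then hours gives the following SDs:
- Hours even 0-10: confidence 0.04 (0.21 as planned), hours 0.18 (0.21 as planned).
- Skewed confidence, mean 3 h: confidence 0.05 (0.21), hours 0.20 (0.23).

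The gain is large on confidence and modest on hours, because a triplet that straddles two confidence levels joins the longest hours of one to the shortest of the next.

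**The case against.** The main objection is to the reading. The whole-hour phrase sits parallel to the five-point-scale phrase and may describe how training is recorded, not how wide a stratum is. The Abstract speaks of experience level, and a condensed article may leave cut-points to the full protocol. That stands as a doubt, but the article states no bands and says blocks are run within each stratum, so whole hours are the natural reading. Banding alone would not settle it: even 2x2 strata reach 24/24/24 only about 31% of the time, 3x2 about 20%, and a skewed 3x3 grid about 14%.

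Several stronger inferences are tempting, and the documents do not support them:

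- *Most blocks will be incomplete.* That depends on an hours distribution that is not given, and it fails if most applicants are novices.
- *The scheme balances badly.* It does better than simple randomisation in these simulations and falls short only of what a better scheme could do.
- *Confidence and hours are the strongest predictors of outcome, so the noninferiority comparison is compromised.* Nothing in the article ranks predictors. The primary analysis adjusts for baseline score on the same task, which offsets part of any imbalance. Randomisation remains valid and no bias is shown.
- *Some arm almost always overflows (94-98% in simulation).* That count includes CBL, which has no seat limit.
- *Participants will have to be reassigned.* The article does not say so. The platform is described as optimised for 24, not capped there. The average VCT excess is only about 0.6-1.2 people, and VCT exceeds 26 in about 4-21% of runs.

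**Conclusion.** The concern holds in a limited form. Followed literally, the allocation rule usually misses the 24 per arm fixed in Sample Size and the teaching ratios built on it in Interventions, and the article gives no rule to reconcile them. An exact split has a chance of about 2-8% under plausible spreads and about 15-30% if nearly everyone is a novice. VCT or FFT is above 24 in about 60-75% of allocations under most spreads. These figures assume whole-hour strata, independent blocks in each, and distributions of confidence and hours that the documents do not supply. The exact percentages move with those assumptions; the conclusion that a 24/24/24 split is the exception does not.

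The harm is mainly to delivery and to clarity about what happens when an arm overfills. The statistical cost is small: about 1-5% in the standard error and some avoidable imbalance in experience. Moderate severity, not a must-fix.

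**What to change.** All 72 are selected before allocation, so the list can be randomised in one step. Sort it by confidence and then by prior hours (ties in random order), cut it into 24 consecutive triplets, and randomise one member of each triplet to each arm. This keeps the block of 3 and guarantees 24 allocated per arm. Reversing the hours order in alternate confidence levels removes most of the mismatch in triplets that straddle two levels.

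Give each replacement the slot of the person replaced. Delivered arms can still fall below 24 if no replacement is found.

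If strata are kept, state the hour bands and how incomplete blocks are handled, and accept that coarse bands alone do not guarantee 24.

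The cost is a few lines of allocation code and a sentence in the protocol, with no added participants or procedures.

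The Results section says that data collection has started, so allocation may already have been run. In that case, report the actual arm sizes, the strata used and any reassignment, and add confidence and prior hours as covariates in the ANCOVA, recorded as a change to the statistical plan. That costs two model terms.
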